Recent advancements in robotics and wearable technologies have opened new avenues for restoring movement in neurologically impaired individuals. Over the past 5 years, pediatric exoskeleton systems have progressed considerably, with improvements in adaptive joint actuation, trajectory control, and real-time feedback mechanisms that enhance both safety and engagement (9). Robotic exoskeletons and powered orthoses offer the potential to provide task-specific, repetitive, and intensive gait training while minimizing therapist workload (10). Such devices have shown promise in adult populations with spinal cord injury and stroke (11), and early-stage trials have extended these technologies to pediatric neuromuscular disorders, including CP (12). However, empirical data on the feasibility, safety, and efficacy of prolonged robotic gait training in children with GMFCS IV and V classifications are virtually nonexistent.

For children with GMFCS level IV, the clinical goal of robotic-assisted gait training is not to achieve independent ambulation, but to preserve and enhance residual motor capacity. By enabling structured, repetitive upright movement, exoskeleton training may help maintain joint range of motion, stimulate muscle morphology, mitigate secondary complications such as contractures, and foster postural stability. In addition, the experience of supported upright mobility could promote psychosocial benefits, including motivation, engagement, and perceived quality of life. These outcomes, while modest compared with independent walking, are meaningful for improving comfort, health, and participation in daily life.

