### Intervention

2.6

The intervention group will receive robotic-assisted gait training using the RoboCT Pediatric Lower Limb Rehabilitation Robot (RoboCT Limited Co., Hangzhou, China), a pediatric exoskeleton system designed for overground locomotor training. This device integrates real-time motion sensing, adaptive control algorithms, and customizable joint actuation to deliver precise and individualized gait training for children with minimal voluntary motor control. The system includes powered actuators at the hip, knee, and ankle joints, a dynamic body-weight support harness, and multi-axis load and torque sensors for continuous monitoring of movement safety. Trajectory control is achieved through programmable gait cycles, allowing therapists to adjust joint angles, step length, and walking speed according to each child’s tolerance and progression. The device employs closed-loop feedback to ensure smooth movement execution and adaptive support. Safety features include automatic shutdown in response to excessive joint torque, misalignment detection, and redundant harness support. These integrated mechanical and control features ensure that the system can safely deliver task-specific, repetitive gait training in a pediatric population.

Robotic sessions will be conducted three times per week over a period of 24 weeks, with each session lasting approximately 45 min. All sessions will be conducted at a designated training site under the supervision of certified pediatric rehabilitation therapists. Each robotic training session will follow a structured protocol comprising several core components designed to promote safe, progressive, and task-specific gait rehabilitation. Sessions will begin with a brief warm-up period, which includes passive joint mobilization and postural alignment to prepare the child for exoskeletal engagement. Following this, participants will engage in assisted overground walking guided by the device’s programmable gait cycle, which delivers coordinated joint movements to simulate a physiological walking pattern.

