Throughout the session, dynamic weight-shifting mechanisms will be activated to replicate the loading and unloading phases of gait, encouraging proprioceptive stimulation and trunk engagement. The system will allow for incremental adjustment of walking speed and step length, calibrated weekly to match each child’s individual tolerance and therapeutic progression. In parallel, integrated posture correction and trunk stabilization features will ensure proper alignment and mitigate compensatory strategies during walking.

To enhance engagement and maintain motivation, each session will incorporate a gamified feedback interface that provides real-time visual cues and positive reinforcement. These interactive elements are tailored to pediatric users and are intended to promote adherence through a rewarding, game-like experience. Load-sensing and joint torque feedback systems will continuously monitor safety and fatigue levels, enabling the exoskeleton to adjust support levels as needed. All session data will be digitally recorded to monitor progress and adjust programming parameters weekly.

Participants assigned to the control group will continue their usual care as determined by their caregivers, reflecting real-world rehabilitation practices in China. Usual care may include a combination of home-based stretching, passive range-of-motion exercises, school-based physiotherapy, or conventional outpatient therapy. To enhance comparability, all components of usual care (type, frequency, and duration) will be systematically documented at baseline and monitored during monthly check-ins. Analyses will include sensitivity and subgroup comparisons according to the type and intensity of usual care received. This approach allows us to preserve ecological validity while ensuring that outcome differences are not solely attributable to a weak or poorly defined comparator condition.

No co-interventions or crossovers between groups will be permitted during the intervention phase. Any adverse events, safety concerns, or deviations from the planned robotic training sessions will be logged and reviewed by the clinical monitoring team.

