Passive ankle joint range of motion (ROM) will be measured using an isokinetic dynamometer. The ankle was selected as the primary joint of interest because equinus contracture and limited dorsiflexion represent the most prevalent and clinically consequential deformities in children with GMFCS level IV CP. Restricted ankle mobility directly impacts orthosis fitting, postural alignment, and the ability to engage in supported upright activity. While contractures at the knee and hip are also common, reliable standardized measurement of these joints in this severely impaired population poses methodological challenges and would substantially increase participant burden. For these reasons, ankle ROM was prioritized as a sensitive, feasible, and clinically meaningful outcome measure. Each child will be seated with the knee fully extended, the ankle joint aligned with the dynamometer’s rotational axis, and the foot securely fixed to a footplate. Passive dorsiflexion and plantar flexion will be conducted through full available range to determine ROM and passive torque.

Muscle morphological properties of the lower limbs will be assessed via ultrasonography using a 6–12 MHz linear transducer (Meinianda BX-5, Zibo, China). Images will be acquired for the rectus femoris, quadriceps femoris, and medial gastrocnemius on both lower limbs. Standardized anatomical landmarks will be used for probe placement, and muscle thickness and muscle fascicle length will be quantified offline by blinded assessors.

Psychological satisfaction and treatment engagement will be evaluated using the Pediatric Quality of Life Inventory (PedsQL™ 3.0 NMM), which is validated for children with chronic motor impairments (17). This instrument includes child self-report and parent-proxy versions and assesses multiple dimensions including physical functioning, communication, and emotional well-being. Higher scores represent better perceived quality of life and satisfaction with daily function.

All outcome assessments will be performed at baseline (week 0), mid-point (week 12), and post-intervention (week 24), except for ultrasound imaging, which will be performed only at pre- and post-intervention timepoints.

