### Ethics and dissemination

2.9

This study protocol has been reviewed and approved by the Ethics Committee of Hunan Normal University (approval number: 2025–506) and will be conducted in accordance with the ethical principles outlined in the Declaration of Helsinki. The trial protocol was prospectively registered in the ClinicalTrials.gov under registration number NCT07049523, dated July 2, 2025.

The intervention poses minimal risk to participants. The robotic exoskeleton system is clinically approved for pediatric rehabilitation and is equipped with comprehensive safety mechanisms, including load-sensitive shutdowns and postural supports. All sessions will be supervised by trained rehabilitation specialists to ensure safe operation. Participants in the intervention group may experience temporary fatigue or discomfort, but serious adverse effects are not anticipated. The potential benefits include improved gait performance, joint mobility, and psychological well-being in children with GMFCS level IV CP, a group that currently lacks access to high-intensity ambulatory interventions. Participants in the control group will not be restricted from pursuing usual care.

All personal data collected during the study will be handled in strict confidence. Participants will be assigned anonymized identification codes, and any linkage to identifiable information will be securely stored and accessible only to the principal investigators. Paper forms will be stored in locked cabinets, and electronic data will be stored on encrypted, password-protected servers. Data access will be limited to authorized research personnel. Final datasets used for statistical analysis will be fully de-identified.

The results of this trial will be disseminated regardless of the direction or statistical significance of findings. Findings will be submitted for publication in peer-reviewed, open-access journals specializing in pediatric rehabilitation, neurodevelopmental disorders, or assistive technologies. In addition, study results will be presented at national and international conferences in pediatric neurology, rehabilitation medicine, and assistive robotics. A plain-language summary of key findings will be prepared and shared with participating families and local rehabilitation centers. No participant-identifying information will be included in any reports or publications.

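### Adverse events have no ascertainment described as common to both arms (about 80 contacts against 8), so raw counts by arm would tend to be inflated in the robot arm

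*Protocol article*

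**What the plan says.** **Robot arm.** Section 2.6: "Robotic sessions will be conducted three times per week over a period of 24 weeks, with each session lasting approximately 45 min". Also: "All sessions will be conducted at a designated training site under the supervision of certified pediatric rehabilitation therapists". The same section adds continuous load and torque monitoring and a digital record of each session.

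**Control arm.** The usual-care paragraph of section 2.6 says that "all components of usual care (type, frequency, and duration) will be systematically documented at baseline and monitored during monthly check-ins". No other content is given for those check-ins.

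**Adverse events.** The only sentence on collecting them closes section 2.6: "Any adverse events, safety concerns, or deviations from the planned robotic training sessions will be logged and reviewed by the clinical monitoring team". It names no arm, and gives no method or schedule for asking.

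**Outcomes.** Section 2.7 names gross motor function and walking capacity as primary, and ankle range of motion, muscle morphology and psychological satisfaction as secondary. No harm is listed. Both arms attend assessments at weeks 0, 12 and 24, described for these outcomes only.

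**Safety background.** The Introduction states that "empirical data on the feasibility, safety, and efficacy of prolonged robotic gait training in children with GMFCS IV and V classifications are virtually nonexistent". Section 2.9 (Ethics and dissemination) states: "The intervention poses minimal risk to participants", and later: "Participants in the intervention group may experience temporary fatigue or discomfort, but serious adverse effects are not anticipated".

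**The concern.** The chance that an event is recorded depends on how often someone who would record it sees the child or speaks to the family. As described, that chance differs about tenfold between the arms. Events that these children have anyway, such as pain, falls or skin problems, would then be written down more often in the robot arm even if the robot caused none of them.

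Two consequences follow. A table of events by arm, which readers of a randomized trial will compare whether or not a comparison was planned, would lean against the robot. And without a comparable control rate, robot-arm events cannot be separated from background events, so a real signal could be put down to closer observation. Neither can be repaired in the analysis, because control-arm events that nobody asked about are lost. This matters here because the article itself names safety as a gap in the evidence.

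**Working it through.** The article gives no figure for harms or contacts, so there is none to reproduce. The arm size used below, 36 / 2 = 18, comes from section 2.4.

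**1. Contacts**

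- Robot sessions: 3 per week × 24 weeks = 72.
- Monthly check-ins: 24 × 7 / 30.44 = 5.5 calendar months, or 24 / 4 = 6 if four-weekly.
- Sessions against check-ins alone: 72 / 6 = 12, or 72 / 5.5 = 13.
- Post-baseline visits common to both arms: 2 (weeks 12 and 24).
- With check-ins in both arms and the common visits: 72 + 6 + 2 = 80 against 6 + 2 = 8, a ratio of 10.
- If only controls have check-ins, since these appear in the control-group paragraph: 74 / 8 = 9.25.

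**2. What unequal contact could do to a count**

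Assume equal true incidence and a chance *p* that any one contact picks up an event, independently across contacts. The chance of detection over *k* contacts is 1 − (1 − *p*)^*k*. No value of *p* stands in the article, so a range is shown.

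| Assumed *p* | Robot, *k* = 80 | Control, *k* = 8 | Spurious ratio |
|---|---|---|---|
| 5% | 1 − 0.95^80 = 0.983 | 1 − 0.95^8 = 0.337 | 2.9 |
| 10% | 1 − 0.90^80 > 0.999 | 1 − 0.90^8 = 0.570 | 1.8 |
| 20% | 1 − 0.80^80 > 0.999 | 1 − 0.80^8 = 0.832 | 1.2 |
| 50% | > 0.999 | 1 − 0.50^8 = 0.996 | 1.0 |

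The formula treats every event as open to detection at every contact. It shows direction and rough scale only.

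**3. Effect on a test**

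Take 18 children per arm, an assumed true risk of 0.40 in both arms, and assumed overall detection of 0.90 in the robot arm, giving a recorded rate of 0.40 × 0.90 = 0.36.

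| Control detection | Control recorded rate | Ratio | Fisher's test rejects at 0.05 |
|---|---|---|---|
| 0.90 | 0.36 | 1.0 | 2% |
| 0.75 | 0.30 | 1.2 | 3% |
| 0.50 | 0.20 | 1.8 | 11% |
| 0.25 | 0.10 | 3.6 | 33% |

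A false signal becomes common only if control detection is poor.

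**4. A separate limit, set by arm size**

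- Zero serious events in 18: one-sided 95% upper bound 1 − 0.05^(1/18) = 0.153.
- A harm with a true risk of 5% would not appear at all in 18 children with probability 0.95^18 = 0.40.

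These figures do not depend on ascertainment, and equal check-ins would not change them.

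**The case against.** **The article is condensed.** It is based on Protocol Version 1.2, which is not shown and may say how events are solicited. The adverse-event sentence can be read as covering both arms, and a check-in that records usual care may also record events. This stands in part: a reader might infer that control-arm events are not collected, or that events at home are sought in neither arm, and the text supports neither. What the article does state is the contact schedule, the content of the check-ins and the outcome list. A fuller logging procedure would cure the imbalance only if it put the same questions to both arms on the same schedule.

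**No comparison of harms is promised, and minimal risk is an ethics statement, not a hypothesis.** Both are true. A reader might go further and infer that the trial cannot test its minimal-risk statement. That does not follow from unequal contact. The statement concerns the robot arm, which is watched most closely, and under-detection in controls makes the robot look worse, not falsely safe. The limit on reassurance is the 18 children.

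**The inflation may be small.** This stands. Caregivers are likely to recall a fracture or a seizure at any later contact, so *p* is high for such events and the ratio is close to 1. The bias chiefly concerns minor or transient events. No single ratio should be quoted as the expected bias.

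**Unequal contact is inherent in comparing a supervised programme with usual care.** It is, but unequal questioning is not.

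**Conclusion.** The point holds as a cheap improvement to the plan, not as a flaw that undermines the trial. As described, opportunities to record an adverse event differ about 10-fold (12- to 13-fold for sessions against check-ins alone), no common ascertainment is set out, and harms are not a listed outcome. A raw between-arm count would therefore tend to be inflated in the robot arm, and robot-arm events could not be separated from background events.

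The size of the bias is unknown. The ratios of 2.9, 1.8 and 1.2 rest on assumed detection of 5%, 10% and 20% per contact, on independence between contacts, and on check-ins taking place in both arms. The conclusion also assumes that the unseen full protocol does not already ask both arms the same questions on the same schedule.

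Separately, a zero count of serious events in the robot arm would still be compatible with a true risk of up to about 15%.

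**What to change.** 1. In section 2.6, state that one fixed adverse-event question list is put to both arms at the same monthly check-ins and at weeks 12 and 24, in the same manner in each arm.
2. In section 2.7, add adverse events by arm as a secondary outcome.
3. Base any between-arm comparison only on events from these common contacts.
4. List device events noted during robot sessions separately, against the number of sessions delivered.
5. Report zero counts with their upper confidence bound.

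**Cost.** A short form at contacts already planned, and a monthly check-in for the 18 robot-arm children if they do not have one, which can take place at a session they attend. More control-arm events will be recorded. At weeks 12 and 24 someone other than the blinded outcome assessor should ask the questions, since the answers may reveal the allocation. Sample size and treatment are unchanged. Section 2.2 says that nobody had been enrolled at submission, so the change could be made before follow-up begins.

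**What remains.** Families know their allocation, so some difference in reporting may persist even with equal questioning.

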### Outcomes

2.7

The primary outcome of this study will be gross motor function and walking capacity, assessed at baseline, middle-point, and after the 6-month intervention period. Secondary outcomes will include passive ankle joint range of motion, muscle morphological properties, and psychological satisfaction. All assessments will be conducted by trained evaluators blinded to group allocation.

Gross motor function will be evaluated using the Gross Motor Function Measure–Item Set (GMFM-IS), a validated short-form tool derived from the full GMFM-66, appropriate for assessing changes in children with CP (16). It focuses on key motor tasks across five dimensions: lying and rolling, sitting, crawling and kneeling, standing, and walking, running, and jumping. In this study, trained evaluators will observe children as they perform selected motor tasks from the GMFM-IS. Each task will be scored on a 4-point ordinal scale: 0 = does not initiate; 1 = initiates (<10% of the task); 2 = partially completes (10–99%); 3 = completes the task independently. The assessment will take place in a quiet, controlled environment with standardized instructions and safety precautions. Scores will be entered into the Gross Motor Ability Estimator software to generate interval-level total scores, allowing for sensitive tracking of changes in motor function over time.

To assess functional walking capacity, participants will undergo the 1-min walk test, performed on a marked 20-meter indoor course. Children will be instructed to walk as quickly and safely as possible without running, and the total distance covered in 60 s will be recorded. For participants who require orthoses or walkers, such assistive devices will be permitted during testing, consistent with real-world functionality.

Passive ankle joint range of motion (ROM) will be measured using an isokinetic dynamometer. The ankle was selected as the primary joint of interest because equinus contracture and limited dorsiflexion represent the most prevalent and clinically consequential deformities in children with GMFCS level IV CP. Restricted ankle mobility directly impacts orthosis fitting, postural alignment, and the ability to engage in supported upright activity. While contractures at the knee and hip are also common, reliable standardized measurement of these joints in this severely impaired population poses methodological challenges and would substantially increase participant burden. For these reasons, ankle ROM was prioritized as a sensitive, feasible, and clinically meaningful outcome measure. Each child will be seated with the knee fully extended, the ankle joint aligned with the dynamometer’s rotational axis, and the foot securely fixed to a footplate. Passive dorsiflexion and plantar flexion will be conducted through full available range to determine ROM and passive torque.

Muscle morphological properties of the lower limbs will be assessed via ultrasonography using a 6–12 MHz linear transducer (Meinianda BX-5, Zibo, China). Images will be acquired for the rectus femoris, quadriceps femoris, and medial gastrocnemius on both lower limbs. Standardized anatomical landmarks will be used for probe placement, and muscle thickness and muscle fascicle length will be quantified offline by blinded assessors.

Psychological satisfaction and treatment engagement will be evaluated using the Pediatric Quality of Life Inventory (PedsQL™ 3.0 NMM), which is validated for children with chronic motor impairments (17). This instrument includes child self-report and parent-proxy versions and assesses multiple dimensions including physical functioning, communication, and emotional well-being. Higher scores represent better perceived quality of life and satisfaction with daily function.

All outcome assessments will be performed at baseline (week 0), mid-point (week 12), and post-intervention (week 24), except for ultrasound imaging, which will be performed only at pre- and post-intervention timepoints.

### Data management

2.8

Standardized case report forms will be used to record participant data in both paper and electronic formats. Data will be entered into a secure, password-protected database by trained research assistants and verified by a second reviewer to ensure accuracy. Each participant will be assigned a unique identifier to maintain confidentiality, and only de-identified data will be used for statistical analyses.

All data will be checked for completeness at each assessment point. In the case of missing data, a detailed log will be kept to identify the reasons and patterns of loss. If the amount of missing data exceeds 5%, multiple imputation methods will be applied under the assumption that data are missing at random. Sensitivity analyses will be conducted to assess the robustness of findings across imputed and complete-case datasets.

Descriptive statistics will be calculated for all variables to summarize baseline characteristics and monitor participant flow throughout the trial. Continuous variables will be reported as means ± standard deviations (or medians and interquartile ranges if non-normally distributed), and categorical variables will be presented as frequencies and percentages. Between-group differences at baseline will be tested using independent samples *t*-tests, Mann–Whitney U tests, or chi-square tests, as appropriate.

The primary analysis will follow the intention-to-treat principle, including all randomized participants regardless of adherence or dropout status. A repeated measures ANOVA or linear mixed-effects model will be used to evaluate between-group differences in changes over time for the primary outcomes (GMFM-IS scores and 1-min walk test distance). These models will include group (intervention vs. control), time (baseline, week 12, week 24), and a group-by-time interaction term. Subject-level random effects will account for within-participant correlations.

Exploratory subgroup analyses will be performed to examine the potential moderating effects of age group (6–8 years vs. 9–12 years), sex (male vs. female), and initial GMFM-IS baseline scores. These analyses will use interaction terms in the mixed-effects models to assess whether treatment effects differ across strata. Results will be interpreted with caution due to potential reductions in statistical power and the exploratory nature of these comparisons.

All statistical analyses will be performed using R, with a two-tailed alpha level of 0.05 considered statistically significant. A detailed statistical analysis plan will be finalized prior to database lock.

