**Methods:**

This two-arm, parallel-group, randomized controlled trial will enroll 36 children aged 6–12 years with GMFCS level IV CP. Participants will be randomized 1:1 to either the intervention group (robotic gait training using the RoboCT Pediatric Lower Limb Rehabilitation Robot) or the control group (usual care as determined by family preference). The intervention group will receive 45-min sessions, three times per week for 24 weeks. Primary outcomes include Gross Motor Function Item Set and walking capacity (1-min walk test). Secondary outcomes include passive ankle joint range of motion, lower-limb muscle morphology via ultrasound, and psychological satisfaction. Linear mixed-effects models will evaluate group-by-time effects under an intention-to-treat framework.

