### Sample size

2.4

As of the trial planning period in 2025, no randomized controlled trial data are available investigating the effects of robotic-assisted gait training on both gait dynamics and lower-limb muscle function in children with spastic CP classified as GMFCS level IV. Due to the absence of prior randomized controlled trials in children with GMFCS level IV, the effect size for this trial was conservatively estimated based on findings from systematic reviews and meta-analyses in ambulatory children with milder CP (GMFCS I–III). While this introduces some uncertainty, it represents a standard methodological approach in feasibility trials where direct data are unavailable. Reported effect sizes from these studies are consistently large, with Cohen’s d values ranging from 0.8 for gait speed (14) to 1.65 for step length (15) improvements.

Considering the intensive, device-assisted nature of the intervention and the magnitude of improvement observed in related populations, an effect size of Cohen’s d = 1.0 was deemed appropriate for the sample size estimation in this trial. Using G*Power 3.1 software to model a two-tailed independent samples *t*-test with a significance level of 0.05, power of 0.80, and equal group allocation (1:1 ratio), a total of 34 participants (17 per group) were required to detect the hypothesized between-group differences. To accommodate a potential 5% dropout rate, the final recruitment target has been adjusted to 36 participants, ensuring adequate power to detect meaningful effects while accounting for minimal attrition.

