### Randomization and blinding

2.5

Participants will be randomly assigned in a 1:1 ratio to either the intervention group (robotic gait training) or the control group (usual care) using a computer-generated randomization sequence. The allocation sequence will be generated using a random number generator in R (package randomizr version 1.0.0) to ensure allocation concealment. Block randomization with a fixed block size will be employed to maintain balance between the groups throughout the recruitment period.

The assignment will be managed by a researcher not involved in participant enrollment or outcome assessment. Group allocation will be revealed to participants and caregivers following enrollment due to the nature of the intervention, which precludes participant-level blinding. This trial will follow a single-blind design, in which the statistician performing the primary and secondary analyses will remain blinded to group allocation until all data collection and preliminary data checks are complete. All outcome assessors collecting GMFCS scores, gait parameters, ultrasound muscle measures, and psychological questionnaires will remain blinded to group allocation to minimize detection bias. In the event that unintentional unblinding occurs, this will be documented, and an independent statistician—who is not otherwise involved in the trial—will be invited to conduct additional sensitivity analyses to ensure the robustness of the findings.

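### The primary analysis is left open between two methods and no primary time point or contrast is fixed; name one baseline-adjusted mixed model with a single week-24 test

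*Protocol article*

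**What the plan says.** Section 2.8 (Data management) gives the primary analysis as follows: "A repeated measures ANOVA or linear mixed-effects model will be used to evaluate between-group differences in changes over time for the primary outcomes". On the model terms it says: "These models will include group (intervention vs. control), time (baseline, week 12, week 24), and a group-by-time interaction term". It adds subject-level random effects, lists no baseline covariate, and promises that all randomised children are included whatever their adherence or dropout. Multiple imputation applies only if more than 5% of data are missing.

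The Methods paragraph of the abstract names one method only: "Linear mixed-effects models will evaluate group-by-time effects under an intention-to-treat framework".

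Section 2.7 (Outcomes) lists three assessments of the two primary outcomes and marks none as primary. Section 2.4 (Sample size) bases the number on a simple two-group comparison ("Using G*Power 3.1 software to model a two-tailed independent samples" t-test) with Cohen's d = 1.0. It does not tie d to an outcome, a time point or a particular SD.

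On timing, section 2.5 says the statistician "will remain blinded to group allocation until all data collection and preliminary data checks are complete", and section 2.8 says "A detailed statistical analysis plan will be finalized prior to database lock".

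**The concern.** Three things are left loose that a confirmatory analysis needs to pin down.

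- **The method.** The body and the abstract disagree, and the two methods are not interchangeable. A conventional repeated measures ANOVA uses only children with every visit; a mixed model uses whatever visits a child has.
- **The comparison.** With three time levels, the group-by-time term has 2 degrees of freedom and asks whether the profiles differ anywhere. A gain at week 12 that has gone by week 24 counts as a difference. The sample size rests on a 1-df comparison of two means.
- **The use of baseline.** With baseline as a response level and a free group effect, the week-24 comparison is in effect a change score. Adjusting for the baseline already collected would be more precise.

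At stake is whether a significant result would answer the question of a 24-week programme, and how much choice the analyst keeps.

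**Working it through.** **Inputs from the protocol article:** d = 1.0, two-sided alpha 0.05, power 0.80, 17 per group, 5% dropout, target 36 (section 2.4); time at baseline, week 12 and week 24 (section 2.8).

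**Assumed, because the article gives no figure:** correlation ρ between visits from 0.3 to 0.9, equal for all pairs of visits (compound symmetry), and equal variances.

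**1. The plan's own figure.** Exact two-sample t-test power at d = 1.0 is 78.1% with 16 per group and 80.7% with 17. So 17 per group is right, and 34 / 0.95 = 35.8, rounded up to 36. The sample size reproduces.

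**2. The overall group-by-time test.** With n = 17 per arm, the F test has 2 and 2 × (34 − 2) = 64 df. Its noncentrality is λ = (n/2) × Σ(e − ē)² / (1 − ρ), where e is the group difference at weeks 0, 12 and 24 in outcome SDs. A change score has SD √(2(1 − ρ)) outcome SDs. So if e is in change-score SDs, λ = n × Σ(e − ē)², and ρ drops out.

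With effects in change-score SDs:

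| Effect at weeks 0, 12, 24 | Σ(e − ē)² | λ | Chance of a significant interaction |
|---|---|---|---|
| 0, 0.5, 1 (linear build-up) | 0.50 | 8.50 | 72% |
| 0, 0, 1 or 0, 1, 1 | 0.667 | 11.33 | 85% |
| 0, 1, 0 (week 12 only) | 0.667 | 11.33 | 85% |
| 0, 0.5, 0 (week 12 only) | 0.167 | 2.83 | 29% |

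In the two week-12-only rows, a week-24 change contrast would reject about 5% of the time.

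**3. The same test with d in outcome SDs.** For the linear build-up, λ = 4.25 / (1 − ρ):

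| ρ | λ | Power |
|---|---|---|
| 0.3 | 6.07 | 57% |
| 0.5 | 8.50 | 72% |
| 0.7 | 14.17 | 92% |
| 0.8 | 21.25 | 99% |

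The power therefore depends on which SD is meant, and the article does not say. Simulation (20,000 runs per setting) agreed under compound symmetry. With correlation decaying over time (AR(1)) and ρ = 0.7, the linear build-up gave 80% for the ANOVA F test and 69% for the unstructured test.

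**4. Baseline adjustment.** The variance of the baseline-adjusted week-24 difference, relative to the change-score difference, is (1 − ρ²) / (2(1 − ρ)) = (1 + ρ)/2. With d = 1.0 change-score SD, the effective d becomes √(2/(1 + ρ)):

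| ρ | Variance ratio | Reduction | Effective d | Power at 17 per arm |
|---|---|---|---|---|
| 0.5 | 0.75 | 25% | 1.155 | 90% |
| 0.7 | 0.85 | 15% | 1.085 | 86% |
| 0.8 | 0.90 | 10% | 1.054 | 85% |
| 0.9 | 0.95 | 5% | 1.026 | 83% |

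The change-score comparison has 80.7% on this scale.

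**5. Missing visits.** Below the imputation trigger, a conventional repeated measures ANOVA drops any child with a missed visit. Counted by children, one of 36 is 2.8%, under the trigger; two of 36 is 5.6%, over it. Counted by visits, 36 × 3 = 108 per outcome and 5% is 5.4, so up to five missed visits stay under it. The article does not say which count applies.

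**The case against.** Much of the case for the defence stands.

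- **Week 24 as the powered comparison.** A reader might infer that the trial was powered at week 24 and analysed otherwise. Section 2.4 names no time point, so the text shows only that none is fixed.
- **The 2-df test as decision rule.** A reader might infer this from the abstract. No section says so. The same model yields a week-24 contrast, and the choice could be made in the promised SAP.
- **A general loss of power.** This is not shown. The interaction test falls short under some effect patterns and scales and exceeds 80% under others. The 85% scenario is also extreme: training runs throughout the 24 weeks, and nothing in the article predicts a full effect at week 12 that vanishes by week 24.
- **Bias from not adjusting for baseline.** There is none. The model compares changes from baseline, which is unbiased under randomisation. The cost is precision only, and it is small at high correlation.
- **Breach of intention to treat.** This is limited to missing data at or below 5%; above that, imputation completes the data for either method. The random effects and the subgroup wording in section 2.8 also point towards the mixed model.
- **Model choice made unblinded.** The wording on blinding and on the SAP permits this order of events. It does not state it.

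What the defence does not answer is that the body contradicts the abstract on the primary method, and that neither the design nor the analysis text says which comparison decides the trial.

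**Conclusion.** The point holds as a should-fix. The protocol article contradicts itself on the primary method and fixes no primary time point or contrast, and its d = 1.0 is attached to no outcome, time point or SD. If the overall interaction were used as the test, a positive result would not by itself show benefit at 24 weeks, and the true power could lie on either side of 80%. Adjusting for baseline would cut the variance of the week-24 change comparison by 5% to 25% for correlations of 0.9 to 0.5, at no cost.

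All power figures rest on 17 per arm and on assumed visit correlations; the main ones also assume compound symmetry. The sample-size arithmetic is correct.

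**What to change.** 1. In section 2.8, delete the repeated measures ANOVA alternative so that the text agrees with the abstract.
2. State one mixed model for the week-12 and week-24 values, with the baseline value as covariate, group, visit and group-by-visit. A model that keeps baseline in the response but constrains it equal across arms is an acceptable alternative.
3. Make the 1-df adjusted group difference at week 24 the primary test, with week 12 supportive.
4. In section 2.4, state which outcome, time point and SD d = 1.0 refers to.
5. In sections 2.5 and 2.8, state that the SAP is finalised before the statistician is unblinded.

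The cost is wording only: no extra children, visits or measurements. Section 2.2 reports that nobody had been enrolled when the manuscript was submitted.
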